**Sample size/power calculation**

The main analysis is on opiate substation treatment (OST) in primary care and risk of death and in particular the comparison of methadone and buprenorphine*.

There will be at least 20,000 OST patients (extracted from CPRD GOLD patients) from 1998 to 2014 linked to NHS central registry and ONS mortality data, that will generate 67,000 person years (pys) follow-up (~32,000 on treatment and ~35,000 off) if censored 12 months after last OST. There will be over 700 deaths of which ~500 will be due to overdose. This will be the largest study in the UK with precise data on OST treatment exposure (including ~ 12000 pys on buprenorphine and 30,000pys on methadone). In addition, there will be approximately 10,000 and 12,000 person years in treatments lasting less than 1 month or greater than 12 months, and 3000 and 1200 person years follow-up in the first 4 weeks treatment on or immediately after methadone or buprenorphine treatment respectively.

Thus, there is sufficient power (> 90%) to determine whether:-

1. there is at least a halving of the risk of death during treatment on burpenorphine compared to methadone (i.e. 0.35% vs. 0.69% respectively) – which requires a sample of at least 922 in each group compared to 12,000 and 20,000 on buprenorophine and methadone
2. and sufficient power (80%) to test if the risk of death is at least a 1/3 lower on buprenorphine at (0.006%) compared to methadone (0.016%) in the first 4 weeks of treatment (1200 and 3000 person years respectively) – as indicated by unpublished analyses by Degenhardt on Australian mortality cohort(9).

In addition, there is sufficient power to corroborate that the risk of fatal overdose out of treatment at 0.8% is twice as high as the risk during treatment – which will require sample of at least 788 in and out of treatment compared to our sample of over 30,000 person years in each group; and that the risk of death in the 4 weeks after treatment at about 4.6% is 1/3 lower (3.0%) for people treated for short duration of treatment (< 1 month) compared to those treated for 12 months or longer – which will require sample of at least 3123 in each group compared to over 3500 and 3850 person years among those exposed to short or prolonged treatment respectively;

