**Study population**

The study population comprise all patients aged 16-64 who have been prescribed methadone or buprenorphine as opiate substitution treatment (OST) in CPRD practices from 1997 to 2014, including a sub-set of patients eligible for ONS linkage. opiate dependent people treated with opiate substitution drugs on CPRD. The table shows the initial set of criteria. Prescription dose and diagnoses will be checked to confirm that prescription for OST and to exclude any patients prescribed for pain/analgesia.

| **prodcode** | **Productname** |
| --- | --- |
| 3064 | Buprenorphine 400microgram sublingual tablets sugar free |
| 3522 | Temgesic 200microgram sublingual tablets (RB Pharmaceuticals Ltd) |
| 6056 | Buprenorphine 8mg sublingual tablets sugar free |
| 6210 | Subutex 8mg sublingual tablets (RB Pharmaceuticals Ltd) |
| 6547 | Buprenorphine 2mg sublingual tablets sugar free |
| 7457 | Temgesic 0.3mg/ml Injection (Reckitt Benckiser Healthcare (UK) Ltd) |
| 8017 | Temgesic 400microgram sublingual tablets (RB Pharmaceuticals Ltd) |
| 10077 | Subutex 2mg sublingual tablets (RB Pharmaceuticals Ltd) |
| 13031 | Subutex 0.4mg sublingual tablets (RB Pharmaceuticals Ltd) |
| 35269 | Temgesic 300micrograms/1ml solution for injection ampoules (RB Pharmaceuticals Ltd) |
| 40211 | Buprenorphine 2mg sublingual tablets sugar free (Teva UK Ltd) |
| 40212 | Buprenorphine 8mg sublingual tablets sugar free (Teva UK Ltd) |
| 40473 | Buprenorphine 300micrograms/1ml solution for injection ampoules |
| 35169 | Suboxone 8mg/2mg sublingual tablets (RB Pharmaceuticals Ltd) |
| 35170 | Suboxone 2mg/500microgram sublingual tablets (RB Pharmaceuticals Ltd) |
| 35681 | Buprenorphine 2mg / Naloxone 500microgram sublingual tablets sugar free |
| 35682 | Buprenorphine 8mg / Naloxone 2mg sublingual tablets sugar free |
| 38311 | Naloxone hc 2mg + 8mg Tablet |
| 42074 | Naloxone hc 500micrograms + 2mg Tablet |
| 2952 | Methadone 1mg/ml oral solution |
| 5211 | Methadone 2mg/5ml linctus |
| 5322 | Physeptone 5mg tablets (Martindale Pharmaceuticals Ltd) |
| 6441 | Methadone 5mg tablets |
| 9728 | Methadone 1mg/ml oral solution sugar free |
| 11722 | Methadone 10mg/ml oral solution sugar free |
| 14086 | Methadone 10mg/ml Injection |
| 17671 | Methadone 50mg/1ml solution for injection ampoules |
| 17896 | Physeptone 10mg/ml Injection (Martindale Pharmaceuticals Ltd) |
| 21562 | Physeptone 1mg/ml mixture sugar free (Martindale Pharmaceuticals Ltd) |

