*Main outcome:* All and cause specific death (in particular drug poisoning/overdose) during drug treatment or follow-up period up to one year after date of last opiate substitution treatment (OST) prescription/treatment admission. Standard codes for drug related poisonings deaths will be used to define overdose deaths (23): ICD-10 codes: F11-16; F18-19; X40-44; X60-64; X85; Y10-14; as well as in terms of general and specific drugs mentioned on the death certificate (any opiate, heroin and Morphine, Methadone, buprenorphine, dihydrocodeine, other opiods, cocaine, all amphetamines and MDMA, GHB, GBL, all benzodiazepines, barbiturates, all antidepressants, paracetamol and other over the counter medicines). We will categorise deaths as “avoidable” and “preventable” based on ONS definitions (<http://www.ons.gov.uk/ons/publications/re-reference-tables.html?edition=tcm%3A77-262418>). Other specific causes that will be investigated include suicide and other injury (non drug related poisoning), infectious diseases, cirrhosis and liver disease. All cause mortality will be expressed as a rate and as a Standardised Mortality Ratio (SMR) compared to standard age and sex death rates for England and Wales. Cause specific mortality will be expressed as rates – and SMRs also will be calculated for non-drug related poisonings. Follow-up of patients extracted from primary care database (Clinical Practice Research Datalink, CRPD) will be from date of first OST prescription within risk period beginning 1990 to end 2011. A patient’s follow up will cease either one year after the expiry of their last prescription for OST or the date of death or on the date of transfer out from the general practice or risk study period end (which ever date occurs first). [Follow-up of patients extracted from Drug Data Warehouse (DDW) will be from 2005 to 2009 the period for which National Drug Treatment records are linked to the mortality register.] We are censoring follow-up twelve months after last prescription or specialist drug treatment date in order to reduce potential bias.

Secondary outcomes concern the practice and delivery of OST including:- annual number of people in OST; modality/specific OST drug; duration of OST; dose; evidence of reaching optimal dosage, tapering OST dose towards planned discharge, and supervised consumption; and co-prescription of benzodiazepines.

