**Study population**

Data extraction comprises all patients aged 16-64 who have been prescribed methadone, buprenorphine or dihydrocodeine in CPRD practices from 1997 to 2014. Patients solely prescribed dihydrocodeine will require additional evidence of drug addiction. This will include a sub-set of patients eligible for ONS linkage.

Patients prescribed methadone or buprenorphine will be identified from the following product codes.

Additional patients will be identified based upon prescriptions for dihydrocodeine using the following list of product codes

and evidence of drug addiction from the following list of medcodes.

The study population will be a subset of the data extraction based upon prescription dose and diagnoses to confirm that prescriptions were for opiate substitution treatment (OST) and to exclude any patients prescribed for pain/analgesia.

AMENDMENT 9^th^ December 2015

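### The CPRD follow-up rule ends at the close of 2011, but the study population, the extraction and the power basis all run to 2014

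*Protocol*

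**What the plan says.** The protocol dates the CPRD cohort in four places.

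- **Exposures, outcomes and covariates, Main outcome:** follow-up "will be from date of first OST prescription within risk period beginning 1990 to end 2011". It stops one year after the last OST prescription expires, at death, or "on the date of transfer out from the general practice or risk study period end (which ever date occurs first"). The end of the risk period is therefore a censoring date for every patient.
- **Sample size/power calculation:** at least 20,000 OST patients "from 1998 to 2014 linked to NHS central registry and ONS mortality data, that will generate 67,000 person years (pys) follow-up", split as about "32,000 on treatment and ~35,000 off) if censored 12 months after last OST". It adds: "There will be over 700 deaths of which ~500 will be due to overdose".
- **Study population (main text):** patients prescribed OST "in CPRD practices from 1997 to 2014, including a sub-set of patients eligible for ONS linkage".
- **Study population (amendment of 3 November 2014):** extraction of patients who "have been prescribed methadone, buprenorphine or dihydrocodeine in CPRD practices from 1997 to 2014".

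The amendment of 9 December 2015 (Use of linked data) reports that the linked data supplied in 2014 held fewer deaths than expected and left the analyses underpowered. It requests a new linkage covering more practices and a longer time span. It does not change the follow-up rule.

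**The concern.** The first three of these passages are current main text, and the November 2014 amendment agrees with the study population section. So this is not a difference between live and superseded wording. An analyst who builds the cohort from the Main outcome paragraph stops at the end of 2011. One who builds it from the sample size section continues to 2014. The two get different person-years, deaths and estimates.

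The follow-up rule is the one that acts on the data, because it censors. If it is applied, the last three extracted years add nothing, and the person-years and deaths quoted for power do not describe the cohort analysed. It would also throw away whatever later time the 2015 linkage was obtained to provide. At the other end, the risk period opens in 1990, seven years before the earliest date in the population and extraction sections.

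**Working it through.** **1. The windows.** 1990 to 2011 spans 22 calendar years, 1998 to 2014 spans 17 and 1997 to 2014 spans 18. The follow-up rule overlaps the power window in 14 years (1998 to 2011) and the extraction window in 15 (1997 to 2011). In both cases 2012 to 2014 is lost.

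**2. The plan's own figures.** The person-years add up: 32,000 + 35,000 = 67,000. They cannot be tied to any calendar window, because the protocol gives no annual counts.

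Power is the normal approximation for two proportions, Φ[(|p1 − p2| − 1.96·SE0)/SE1], where SE0 uses the pooled variance and SE1 the separate variances. A two-sided alpha of 0.05 is assumed, since none is stated, and person-years stand in for the group sizes, as in the protocol.

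- On treatment, 0.35% against 0.69% with 12,000 and 20,000: (0.0034 − 1.96 × 0.000864)/0.000796 = 2.15, so power is 98.4% (stated: above 90%).
- First 4 weeks, 1,200 and 3,000 person-years: the printed rates are 0.006% and 0.016%. Taken literally they give about 2% power. Read as 0.6% and 1.6%, (0.010 − 1.96 × 0.00389)/0.00320 = 0.74, so power is 77% (stated: 80%). The second reading comes close to the protocol's claim and is used below, but it is a 100-fold rescaling of what is printed.

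**3. Share kept if follow-up stops at the end of 2011.** Two accrual assumptions, neither taken from the protocol:

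- Even accrual: 14/17 = 0.824, or 15/18 = 0.833.
- Linear growth from zero at the start of 1998: (14/17)² = 0.678.

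**4. Consequences.** Person-years, deaths and group sizes are multiplied by the share kept.

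| | As stated | Even accrual | Linear growth |
|---|---|---|---|
| Person-years | 67,000 | 55,200 to 55,800 | 45,400 |
| Deaths (from 700) | 700 | 576 to 583 | 475 |
| Overdose deaths (from 500) | 500 | 412 to 417 | 339 |
| Power, on treatment | 98.4% | about 96% | 92% |
| Power, first 4 weeks (rates read as 0.6% and 1.6%) | 77% | about 68% | 58% |

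If the share kept is varied from 60% to 90%, person-years run from 40,200 to 60,300 and deaths from 420 to 630. On-treatment power runs from 88% to 97%, and first-4-weeks power from 52% to 72%.

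**The case against.** **The windows may describe different sets.** The 1998 to 2014 figure is attached to the ONS-linked sample, while 1997 to 2014 covers a wider population of which only part is linkable. That can explain 1997 against 1998. It cannot explain 2011 against 2014.

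**The 1990 opening may be harmless.** The population and extraction sections select patients prescribed from 1997. They do not say that earlier records of those patients are dropped. This stands: the documents do not show that the risk period opens on empty data, only that its start differs from the other sections without explanation.

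**The power basis has already been overtaken.** The December 2015 amendment says the expected deaths were not found, with only 30% of deaths overdose or drug related. So the fall from 700 deaths is a fall from a figure already known not to hold. This also stands, and the table should be read as the internal inconsistency of the protocol, not as a forecast. It does not remove the conflict, since the remedy chosen is a longer span that the follow-up rule would cut.

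**The main comparison is hardly touched.** Correct under both accrual assumptions. A reader might infer that ending in 2011 leaves the whole study underpowered. On the stated inputs the on-treatment contrast stays above 90%, and only the first-4-weeks contrast moves materially, on a rescaled reading of its rates.

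**A stronger reading of the entry rule.** Because follow-up starts at the first OST prescription in the window, a reader might infer that patients already on OST are counted as treatment starters. The protocol does not say so. The Main outcome paragraph fixes when follow-up begins. The Exposure paragraph sets treatment periods separately and expects the CPRD data to show when OST started. A look-back rule is operational detail that an analysis plan may hold, and the documents offer no basis for sizing any dilution. At most, the entry rule does not by itself keep continuing users out of the onset period.

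**Conclusion.** The follow-up rule is wrong as written. Its end date contradicts the sample size section, the study population section and the November 2014 amendment, and it works against the December 2015 linkage. That conclusion needs no assumption.

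The size does. Under the two accrual patterns, roughly 18% to 32% of the stated person-years and deaths would go. The actual share cannot be known without annual counts, and neither pattern is a bound. Linear growth from zero in 1998 is not stated anywhere, although the Background's 5-fold expansion of OST over ten years makes some growth plausible. The statistical harm is limited for the on-treatment contrast. It is more serious for the first-4-weeks contrast, on the condition about its printed rates. The larger practical risk is two irreconcilable cohorts from one protocol.

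**What to change.** Set one start date and one end date for the CPRD cohort, and use them in the sample size section, the study population section, the Main outcome paragraph and the November 2014 amendment text. Define the end as the end of the extracted data or of ONS mortality-linkage coverage, whichever is earlier. Do not fix it at 2014 if the new linkage runs later. If records before the start date are kept to show earlier treatment, say so and separate that from the follow-up window. Then restate person-years, deaths and power for the chosen window, and correct or confirm the printed 0.006% and 0.016%.

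The cost is a text amendment, a recount of person-years and deaths, and a rerun of the power figures. No further data are needed beyond the linkage already requested.

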**Exposures, outcomes and covariates**

*Exposure:-* OST includes methadone and buprenorphine and occasionally dihydrocodeine(6, 11). Intervention exposure is defined by prescribing data collected by primary care practices contributing information through their electronic health record systems to the Clinical Practice Research Datalink (CPRD). This will include information on all prescriptions in primary care plus other information on diagnoses and attendances at primary care and hospital. We will extract information on patients on the basis that they have a drug misuse diagnosis and have been prescribed methadone or buprenorphine. Some patients also may have been prescribed dihydrocodeine as OST – and so we will include these treatment episodes as well. The information provided by CPRD will allow us to establish when OST started, changes in dose or type of OST, and when OST ceased. For each treatment period we will classify different periods “on”/during or “off”/after OST or other drug treatment e.g. 1st 2 weeks of treatment, rest of time on treatment (baseline treatment period), 1st 4 weeks after treatment, and rest of time out of treatment (censored at 12 months after last prescription); as well as measure average OST duration and classify treatment duration (≤ 1 month, 2-6 months, 7-12 months, 12+months).

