**Use of linked data**

We will use link to ONS mortality file for our outcome measures. **Data/ Statistical Analysis Plan**

1) We expect that overdose and drug related mortality risk differs by period of treatment exposure (1-4 weeks treatment start, rest of treatment duration, 1-4 weeks treatment end, 5-52 weeks out of treatment). The main analysis will test whether there is evidence of a difference in mortality risk by modality of OST (methadone vs. buprenorphine) at different periods on and off treatment – and will investigate also mortality risk in relation to additional exposures (co-prescription of benzodiazepines, measures of treatment performance/quality) and confounders (age, gender, co-morbidity as defined by Charlson Index(24), alcohol and mental health problems, treatment episode number, calendar year) all of which have been shown to influence mortality risk(11) (9). However, other potential confounders or factors relating to injecting risk may be missing or incompletely measured in CRPD (such as crack-cocaine use).

We will undertake a series of analyses that aim to incorporate and adjust for confounding.

First, we will use Poisson regression incorporating time varying covariates (such as co-prescription of benzodiazepines, episode and duration of treatment) to describe mortality risks and compare these at different periods on and off treatment and by modality of OST. These analyses will generate incidence rate ratios (IRR) that compare mortality risk for patients on methadone (from week 4 to end of treatment as baseline) to other periods and other forms of OST; will compare mortality rate for key confounders (above); adjust IRR by period on or off treatment for these confounders; and examine specifically whether co-prescription of benzodiazpeines increases the risk of mortality during and after treatment.

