Second, we will undertake analyses of patient characteristics in order to develop and use propensity scores that can be used to balance buprenorphine and methadone exposure groups and test for differences in mortality risk between the groups(25-27). The primary care databases hold a substantial amount of information on the patients’ diagnoses and treatment history as well as information on the practices – too much data to fit as individual covariates. Therefore, we can use these data to generate propensity score matching in order to use the score to reduce selection bias and match the patients exposed either to buprenorphine or methadone or to short or long term treatment(27).

Third, the problem of confounding (known and unknown) also will be addressed using self-controlled case-series (SCCS) methodology in which patients act as their own controls(28), as has been used in other studies of primary care databases(29, 30). In this method the number of events are classified according to the length of the exposure (in period; in and out of treatment) and an estimate of the hazard or incidence rate ratio is derived by conditioning on the number of events over the exposure history(28). Since there is missing information on risk of death prior to exposure only cases that have been exposed are included in the analysis. In addition, time invariant confounders (such as sex, age, underlying health problems) are controlled for implicitly; and time variant confounders can be fitted within the model. [name] and [name] are extending the SCCS method to deal with finite outcomes such as drug related/overdose death, and exposures that may persist (such as opiate substitution treatment) and this study will be a case study on how SCCS can be used with such exposures and outcomes. SCCS has been used for censored events – such as death previously (31, 32) – but classifying the exposure will require methodological development.

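### Ending follow-up 12 months after the last OST prescription counts long off-treatment gaps only for patients who survive to restart, which understates the later off-treatment death rate

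*Protocol*

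**What the plan says.** Three places in the protocol define off-treatment time.

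- **Exposures, outcomes and covariates, Main outcome.** A patient's "follow up will cease either one year after the expiry of their last prescription for OST or the date of death", or at transfer out or study end if that comes first. The stated reason is: "We are censoring follow-up twelve months after last prescription or specialist drug treatment date in order to reduce potential bias".
- **Exposures, outcomes and covariates, Exposure.** After the first four weeks off, all remaining off time falls in one class, "rest of time out of treatment (censored at 12 months after last prescription").
- **Data/Statistical Analysis Plan (which runs on from Use of linked data).** The off-treatment classes are "1-4 weeks treatment end, 5-52 weeks out of treatment". There is no class for time beyond week 52 and no instruction on what happens to it.

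The Sample size/power calculation gives the planned totals: "There will be at least 20,000 OST patients" and 67,000 person-years, about 32,000 on and 35,000 off treatment, conditional on censoring 12 months after the last OST. It puts fatal overdose off treatment at 0.8%, twice the on-treatment risk. The model-projection part of the analysis plan then takes the mortality estimates for periods on and off treatment as inputs to the policy model.

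**The concern.** The rule is set per patient and looks ahead. Take two patients who stop OST on the same day. One restarts after three years: that prescription was not the last, so all three years count as off-treatment time. The other dies in month 20 without restarting: the earlier prescription was the last, follow-up ended at month 12, and the death is not counted. Person-time beyond month 12 of a gap enters the denominator only if the patient survived to restart, and no death can fall in it. This is immortal time.

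The off-treatment rate is therefore too low, and the off/on ratio is biased toward 1. Three things are at stake: the later off-treatment class, the overall on/off contrast (for which the protocol claims power), and the off-treatment rates passed to the policy model, where too low a rate would understate the deaths averted by treatment. The 12-month limit was introduced to reduce bias. Tied to the last prescription, it adds one.

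**Working it through.** **1. The plan's own totals.** 32,000 + 35,000 = 67,000 person-years, as stated. An off-treatment risk of 0.8% at twice the on-treatment risk gives 0.4% on treatment and a true ratio of 2.0. (The 788 per group quoted for this contrast does not follow from 0.8% vs 0.4%. At 90% power, two-sided 5%, those rates need 7,832, or 8,324 with continuity correction; 788 comes from 8% vs 4% with the correction. That is a separate matter and is not used below.)

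**2. How much off time lies in gaps.** Each patient has at most one year of off time after the last prescription.

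- At exactly 20,000 patients: 35,000 − 20,000 × 1 = 15,000 person-years (43%) at least lie between episodes.
- At 25,000 patients: 35,000 − 25,000 = 10,000.

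These figures cover gap time of any length. The first 12 months of each gap are properly at risk; only the part beyond 12 months is immortal, and the protocol does not give it.

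**3. Effect on the rate.** With X off person-years beyond 12 months and a constant off-treatment hazard:

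observed off rate = 0.80% × (35,000 − X) / 35,000; observed ratio = observed off rate / 0.40%.

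| X (assumed) | Share of off time | Observed off rate | Observed ratio |
|---|---|---|---|
| 0 | 0% | 0.80% | 2.00 |
| 2,500 | 7.1% | 0.74% | 1.86 |
| 5,000 | 14.3% | 0.69% | 1.71 |
| 7,500 | 21.4% | 0.63% | 1.57 |
| 10,000 | 28.6% | 0.57% | 1.43 |

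**4. Simulation check.** Alternating on and off spells were simulated for 200,000 patients per scenario: 0.4% per year on, 0.8% per year off, exponential spells, mean time on 0.5 years, observation 1 to 16 years. Gap length and the share of stops never followed by a restart are assumptions.

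| Mean gap (years) | Never restart | Off time beyond 12 months | Ratio, rule as written | Ratio, 12-month cap after every episode |
|---|---|---|---|---|
| 0.25 | 30% | 0.6% | 2.02 | 2.03 |
| 0.5 | 30% | 6.4% | 1.86 | 1.99 |
| 1 | 30% | 21.3% | 1.57 | 2.00 |
| 2 | 30% | 38.1% | 1.26 | 2.03 |
| 1 | 0% | 29.1% | 1.45 | 2.04 |
| 2 | 0% | 46.1% | 1.10 | 2.04 |

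The rule as written is close to unbiased only when nearly all returns are quick. The per-episode cap recovers the true ratio throughout.

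**The case against.** **The analysis plan may already exclude this time.** The 5-52 week class has no room for later gap time, and the exposure sentence is framed per treatment period, so a per-episode limit is a possible reading. If it were applied to every gap, the bias would go. But no sentence drops gap time after week 52, the main-outcome rule is worded per patient, and the person-year totals rest on the last OST. This is a stated rule in conflict with another passage, not a detail left to a statistical analysis plan.

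**The effect may be small.** The sample-size section gives 1,200 + 3,000 = 4,200 person-years for four-week periods. If these are all treatment starts, 4,200 × 13 = 54,600 starts, less 20,000 first starts = 34,600 restarts, and a mean gap of 15,000 / 34,600 = 0.43 years. With exponential gaps the share of gap time beyond 12 months is exp(−1/0.43), about 10%. That is about 1,500 of 35,000 (4%), and the ratio is about 1.9. However, the section describes the 4,200 once as time on or immediately after treatment and once as the first four weeks of treatment. Split equally between the two, it gives 2,100 × 13 = 27,300 starts, 7,300 restarts, a mean gap of 2.05 years, about 26% of off time beyond 12 months and a ratio of about 1.5. The totals cannot settle the size. They are also not fully consistent: 12,000 + 30,000 = 42,000 person-years by drug, against about 32,000 on treatment.

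**The key hypotheses are largely untouched.** This stands. The powered methadone-buprenorphine comparisons are during treatment, and the first four weeks after cessation are counted for everyone.

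**A sensitivity analysis exists.** The Limitations section plans other on/off definitions and an analysis using only the last prescription. These address missing prescription data; they may partly expose the problem but do not repair the main analysis.

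**A stronger reading to avoid.** A reader might infer that the treatment-duration classes share the fault, because the protocol counts "10,000 and 12,000 person years in treatments lasting less than 1 month or greater than 12 months" and proposes to "match the patients exposed either to buprenorphine or methadone or to short or long term treatment". The documents do not support that. The Poisson model names duration as time-varying, the powered duration contrast concerns deaths after treatment ends, when duration is already known, and no on-treatment comparison by completed duration is planned. The matching text only leaves the start of follow-up open.

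**Conclusion.** The point holds for the censoring rule. As written, off-treatment time beyond 12 months is kept only for patients who survive to restart and contains no counted deaths. The later off-treatment rate is understated and the off/on ratio is pulled toward 1. The direction is certain wherever such gaps exist; the size is not. If 0 to 10,000 of the 35,000 off person-years lie beyond 12 months, a true ratio of 2.0 appears as 2.0 down to 1.43. This assumes a constant off-treatment hazard and the protocol's planned totals.

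It would be wrong to infer that 43% of off time is immortal: that share is all gap time, at exactly 20,000 patients. It would also be wrong to infer that the main drug comparison is biased. In the later off-treatment class alone, the drug contrast could shift if long gaps are more common with one drug, but the protocol gives nothing from which to size that.

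**What to change.** State one rule and use it in the Exposure paragraph, the Main outcome paragraph and the Data/Statistical Analysis Plan: at-risk time stops 12 months after the expiry of the final prescription of every treatment episode, or earlier at death, transfer out or study end; a patient who later restarts re-enters at the next OST prescription. The 5-52 week class then describes exactly what is analysed. Recompute the planned off-treatment person-years under this rule and report how much gap time is removed.

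The cost is a change to the code that splits person-time and a few sentences. Off-treatment person-years fall, but no counted deaths are lost, because the removed time can hold none.

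As a secondary clarification, state that any matched comparison of short with long treatment starts follow-up at cessation.
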